### Design

Participants will complete a structured 5-week protocol involving four in-person study visits: baseline (t_1_), predosing (t_2_), dosing (t_3_) and postdosing follow-up (t_4_) (see figure 2). At t_1_, they will complete a battery of self-report questionnaires and cognitive tasks assessing psychological wellbeing and inner experience, alongside a 5-minute resting electrocardiogram (ECG) and a saliva sample for cortisol analysis. Participants will be issued a WHOOP wearable device to continuously track biometric data through to t_4_. Between t_1_ and t_2_, participants will engage in the 21-day DIPP. During the 10 days before and after dosing, they will also provide daily voice note samples via the DIPP-bot mobile app for linguistic and acoustic analysis. Further details on the prompt structure and DIPP-bot architecture are provided in online supplemental S7. At t_2_, participants will repeat the battery of questionnaires and cognitive tasks, ECG and saliva sampling from t_1_, and complete a movie-fMRI scan. One day later at t_3_, they will receive a 25 mg dose of psilocybin, with electroencephalogram (EEG) and ECG recorded at baseline (~15 minutes before drug administration), 90 min and 150 min postadministration. Saliva samples will be collected at the same time points for cortisol analysis. At the end of the dosing session, participants will also complete a semi-structured qualitative interview and a battery of validated questionnaires assessing subjective drug effects and phenomenological aspects of the experience**.** At t_4_, participants will complete a semi-structured interview, followed by the battery of questionnaires and cognitive tasks, ECG and saliva sample, and undergo a second movie-fMRI scan. They will also return the WHOOP device, concluding continuous biometric tracking. Remote follow-ups will continue for 9 months, with online assessments and renewed thought sampling via DIPP-bot at 3 (t_5_), 6 (t_6_) and 9 (t_7_) months postdosing.

### Outcome measures

The study employs a comprehensive, multimodal data collection approach, incorporating self-report measures, neurophysiological assessments, behavioural indices and qualitative data. The primary outcomes focus on key indicators of feasibility and adherence, including recruitment efficiency, study retention and engagement (intervention adherence) with DIPP. Recruitment efficiency is measured as the weekly rate of participant enrolment, calculated as the total number of participants successfully completing online screening, researcher screening and clinical screening, divided by the total number of recruitment weeks. Acceptable recruitment efficacy is defined as maintaining an average recruitment rate of at least one participant per week until the target sample of 40 participants is reached. This measure is tracked from study initiation to the completion of recruitment. Study retention is evaluated as the percentage of participants who complete the 2-week post-dose follow-up assessment (t_4_). Acceptable study retention is defined as at least 70% of participants completing the (t_4_) assessment. Intervention adherence will be assessed based on completion of three daily tasks (practice (± guided meditation), mood rating and journal entry) and 2-weekly module-specific tasks, totalling 69 tasks over the 21-day programme (63 daily+6 weekly). Individual adherence is defined as completion of ≥48 tasks (≥70%). Intervention adherence success is defined as ≥70% of participants meeting this individual adherence threshold.^66^ A complete overview of all outcome measures is presented in a SPIRIT table in online supplemental S4, with primary, secondary and other prespecified outcomes detailed in online supplemental S5.

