A core component of DIPP is a daily practice lasting 20–50 minutes, with duration progressively increasing over the 21-day programme. In the **DIPP-MEDITATE** programme, this consists of guided Loving-Kindness Meditation (LKM) delivered over ambient music; in the **DIPP-MUSIC** programme, participants receive the same ambient music without guided meditation instruction (see *Trial Objectives* below). Our previous study, which surveyed meditation practitioners with experience of psychedelic drug use, identified Loving Kindness Meditation (LKM) (inspired by the Theravada Buddhist practice of *mettā bhavana* (in Pāli, the liturgical language))^28 29^ as the most effective practice for psychedelic preparation, significantly outranking meditation approaches based on Focused Attention and Open Monitoring.^30^ Accordingly, LKM serves as the primary meditation technique in DIPP-MEDITATE. The programme systematically cultivates loving-kindness (*mettā*) in three stages: first toward oneself (days 1–7), then extending to another person (days 8–14), and finally expanding outward to encompass all beings (days 15–21).^31^,^33^ Alongside this, participants are introduced to structured methods for working with distractions and refining their meditation practice,^32 33^ including the ‘6Rs’ technique (Recognise, Release, Relax, Re-smile, Return, Repeat)—a cyclical process designed to disengage from distractions in a gentle, non-forceful manner^34 35^—and a framework for recognising different levels of awareness^36 37^ (see online supplemental S1 and S2 for details). These elements support participants in cultivating attentional stability, increasing clarity of awareness and fostering insight into their mental processes,^38^,^40^ thus equipping them with useful skills for navigating shifts in consciousness during psychedelic experiences. A separate publication will provide a detailed account of the meditation framework supporting the DIPP-MEDITATE programme.

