### Trial objectives

To evaluate whether guided meditation substantially contributes to the acceptability, feasibility, and preliminary efficacy of DIPP, we designed a randomised controlled feasibility trial following Standard Protocol Items: Recommendations for Interventional Trials (SPIRIT) guidelines^48^ (SPIRIT table and checklist can be found in online supplemental S4). Forty healthy volunteers will be randomised to DIPP-MEDITATE or DIPP-MUSIC. The trial timeline comprises: baseline (t_1_), pre-dosing (t_2_, day 21), dosing (t_3_, day 22), two-week follow-up (t_4_), and remote follow-ups at 3, 6, and 9 months post-dosing (t_5_–t_7_) (see figure 2).

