### Allocation methods and blinding

Participants will be randomly assigned in a 1:1 ratio to one of two study arms (DIPP-MEDITATE or DIPP-MUSIC) using a random number generator prepared prior to trial commencement. The allocation list will be stored in a secure, password-protected file inaccessible to researchers involved in data collection. A researcher with no involvement in these processes will inform the lead researcher of each participant’s allocation on arrival to enable setup of the appropriate version of the programme.

To minimise expectancy effects, participants are not informed that the study involves randomisation or that there are different versions of DIPP. During the consent process, participants are told they will complete a 21-day digital preparation programme involving daily audio-based activities; no reference is made to different conditions or to the presence of a control group. This incomplete disclosure is necessary to ensure that any observed differences between groups can be attributed to the intervention itself rather than participant expectations. At study completion (t_7_), participants are fully debriefed and informed of the study design and their allocated condition. This procedure was reviewed and approved by the UCL Research Ethics Committee.

Both interventions are matched in structure, interface and schedule. The only difference is the presence or absence of guided meditation within the audio content. All participants will receive standardised instructions (see online supplemental S6) and complete the Credibility and Expectancy Questionnaire^65^ at baseline (t_1_). At the final study visit (t_4_), participants will be asked whether they believe they received the ‘complete DIPP programme’, to assess perceived intervention exposure. As both interventions are fully automated and data will be self-reported, there is no opportunity for researcher influence on outcomes. Any procedural errors leading to inadvertent disclosure of group assignment will be recorded and reported.

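### The primary adherence rule sets no minimum for the daily practice, so adherence success does not show that the guided meditation or the music was used

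*Protocol article*

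**What the plan says.** Under Outcome measures, the Protocol article makes engagement with DIPP one of three primary feasibility outcomes and fixes the rule in full. "Intervention adherence will be assessed based on completion of three daily tasks (practice (± guided meditation), mood rating and journal entry" gives the daily items. Two tasks for each weekly module are added, "totalling 69 tasks over the 21-day programme (63 daily+6 weekly". The individual cut-off follows: "Individual adherence is defined as completion of ≥48 tasks (≥70" per cent). The group criterion is "Intervention adherence success is defined as ≥70% of participants meeting this individual adherence threshold". All tasks carry the same weight, and no minimum is set for any one type of task.

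Three other places say what the practice is for:

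- The Introduction describes its role: "A core component of DIPP is a daily practice lasting 20–50 minutes", with the duration rising over the programme.
- Allocation methods and blinding says of the two arms: "The only difference is the presence or absence of guided meditation within the audio content".
- Trial objectives states why the trial is randomised: "To evaluate whether guided meditation substantially contributes to the acceptability, feasibility, and preliminary efficacy of DIPP".

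Analysis strategy and missing data says that the primary outcomes will be summarised as frequencies and proportions. It specifies a summary by condition for the acceptability and usability scales, but does not say so for adherence.

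**The concern.** The randomised contrast lies wholly inside the practice audio. Mood ratings, journal entries and weekly modules are the same in both arms, yet they supply 48 of the 69 credits. A session of 20 to 50 minutes earns the same credit as one mood rating. A participant can therefore skip much of the practice, make up the count elsewhere, and still be classed as adherent.

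Two conclusions are at stake. The first is feasibility: meeting the criterion could be taken to mean that three weeks of daily guided meditation is workable, when the rule does not test that. The second is the reading of the preliminary efficacy results. If preparedness or acute-experience scores differ little between the arms, the adherence result cannot tell meditation that added little from meditation that was seldom done.

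**Working it through.** **Inputs (Protocol article, Outcome measures).** Programme length is 21 days. There are 3 daily tasks (practice, mood rating, journal entry) and 2 weekly tasks in each of 3 weeks. The individual cut-off is 48 tasks, glossed as at least 70%. The group criterion is at least 70% of participants. The planned sample is 40, 20 per arm (Sample size).

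**Step 1: the plan's own figures.** Total tasks = 3 × 21 + 2 × 3 = 63 + 6 = 69, which agrees with the article. The cut-off does not agree with its gloss: 0.70 × 69 = 48.3, so at least 70% requires 49 tasks (49/69 = 71.0%), whereas 48/69 = 69.6%. The count and the percentage differ by one task.

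**Step 2: split by type of task.** Practice = 21 (21/69 = 30.4%). Other tasks = 21 mood + 21 journal + 6 weekly = 48 (48/69 = 69.6%).

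**Step 3: least practice that passes.** If a participant completes *m* of the 48 other tasks, the sessions needed are 48 − *m* under the stated count, or 49 − *m* under a strict 70%.

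| Other tasks done (of 48) | Sessions needed, cut-off 48 | Sessions needed, cut-off 49 |
|---|---|---|
| 48 (100%) | 0 of 21 (0%) | 1 of 21 (4.8%) |
| 45 (94%) | 3 of 21 (14%) | 4 of 21 (19%) |
| 43 (90%) | 5 of 21 (24%) | 6 of 21 (29%) |
| 40 (83%) | 8 of 21 (38%) | 9 of 21 (43%) |
| 38 (79%) | 10 of 21 (48%) | 11 of 21 (52%) |
| 33 (69%) | 15 of 21 (71%) | 16 of 21 (76%) |

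The one-task discrepancy decides whether zero practice can pass. It hardly changes the rest of the table.

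**Step 4: the plan's 70% standard applied to practice alone.** 0.70 × 21 = 14.7, so 15 sessions are needed (15/21 = 71.4%; 14/21 = 66.7%). At the stated cut-off the composite guarantees this level only when 33 or fewer of the other tasks were done, since 48 − 33 = 15. The more diligent a participant is with the shared tasks, the less the rule says about practice.

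**Step 5: group level.** 0.70 × 40 = 28 participants. If the criterion is read as pooled over arms, which is the plain reading because no arm is mentioned, it could be met with 20 of 20 adherent in DIPP-MUSIC and 8 of 20 (40%) in DIPP-MEDITATE. This illustrates what the rule permits and is not a forecast.

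**The case against.** The strongest reply is that the outcome measures what it claims to measure. The article defines it as engagement with DIPP, and DIPP has several components: practice, mood tracking, journalling and weekly modules. A completion count over the whole programme is a legitimate measure of that. This stands, and the composite should be kept.

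Four stronger readings are tempting but not supported:

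- *Anyone who skips all practice is counted as adherent.* This is true only if all 48 other tasks are completed. One further miss gives 47 and a fail. It also holds only under the count, because under the stated percentage zero practice falls one task short. The article gives no reason to expect this pattern to be common.
- *A null result would be read as showing that meditation adds nothing.* Analysis strategy and missing data says that the study is not powered for group differences and that p-values will not be used for inference. Adherence status does not select any analysis population in the article. Misreading is possible but not built in.
- *The plan contains no practice-specific measure.* The detailed outcome list is in online supplement S5, which is not shown and may include one. That would still not alter the success rule fixed in the article.
- *Practice is the most demanding task.* Its duration is stated, but none is given for journalling or the weekly tasks, so the ranking is an inference.

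These limits narrow the point without removing it. The table shows that moderate diligence with the shared tasks lets well under half of the sessions pass, whichever cut-off is used.

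**Conclusion.** The point holds in a limited form. As fixed in the article, the rule puts no floor under the one component that differs between arms. The least practice compatible with adherence is 0 of 21 sessions at the stated cut-off and 1 of 21 (4.8%) at 49. With 40 of the 48 other tasks done it is 8 of 21 (38%) or 9 of 21 (43%) respectively. Meeting the primary criterion therefore does not show that the guided meditation or the music was used, and on that evidence alone a small between-arm difference cannot be told apart from low uptake.

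This rests on two things that the article states, equal weighting and identical non-practice content across arms, and on nothing about how participants will behave. It does not show that uptake will be low or that the composite is invalid. Separately, the 48-task count and the 70% gloss contradict each other and must be reconciled.

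**What to change.** 1. Reconcile the individual cut-off: 49 of 69 if at least 70% is intended.
2. Keep the 69-task composite as the measure of programme engagement.
3. Prespecify practice-specific adherence, reported by arm beside it: the distribution of sessions completed out of 21, and the proportion of participants with at least 70% of sessions, that is at least 15 of 21. The 15 carries over the plan's own 70% standard and is not a validated exposure threshold.
4. State that adherence to the meditation component will not be claimed from the composite alone.

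If supplement S5 already lists session completion by arm, items 1 and 4 remain, and item 3 becomes a cross-reference plus the 15-of-21 proportion if that is absent.

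Making 15 of 21 a second mandatory success criterion is not needed. It would alter the feasibility decision rule, and reporting by arm already answers the concern.

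The cost is one derived variable from task-level records that the 69-task count already requires, with no added visit, instrument or participant burden. The downside is that the adherence picture may look less favourable. The definition should be fixed before adherence data are examined by arm.

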### Sample size

Because this is a feasibility trial, no formal power calculation was conducted. A sample of 40 participants (20 per group) was chosen based on published guidance for early-phase trials, ensuring sufficient data to assess recruitment, retention and adherence.^49^,^51^

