### Analysis strategy and missing data

This section outlines the analysis plan for primary and secondary outcomes. Exploratory outcomes, including behavioural and neurophysiological measures, will be detailed in separate publications.

Primary feasibility outcomes (recruitment efficiency, study retention and intervention adherence) will be summarised as frequencies and proportions.

Secondary outcomes include a custom Subjective Feasibility of Intervention Scale (SFIS), the Theoretical Framework of Acceptability (TFA),^67^ the System Usability Scale (SUS),^68^ the Mobile Application Rating Scale (MARS),^69^ the Psychedelic Preparedness Scale (PPS),^17^ the Altered States of Consciousness Rating Scale (5D-ASC),^70^ the Challenging Experience Questionnaire (CEQ-7)^71^ and the Short Warwick-Edinburgh Mental Wellbeing Scale (SWEMWBS).^72^ As this feasibility study is not powered to detect between-group differences, analyses are descriptive and exploratory rather than confirmatory. Subjective feasibility and acceptability measures (SFIS, TFA, SUS, MARS) will be summarised descriptively by condition. Linear mixed models will be used to examine change over time for repeated measures (PPS, SWEMWBS), and independent t-tests to compare groups on acute measures (5D-ASC, CEQ-7). Effect sizes and 95% CIs will be reported; p-values may be presented descriptively but will not be used for inference.

For primary outcomes, all available data will be included with no imputation. Linear mixed models accommodate missing data under missing-at-random assumptions. Patterns of missingness will be assessed and reported.

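### The individual adherence cut-off is given as both 48 of 69 tasks and at least 70%, but 48 of 69 is 69.6%, so the two forms disagree for a participant with exactly 48 tasks

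*Protocol article*

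**What the plan says.** Intervention adherence is one of three primary feasibility outcomes in the protocol article (Outcome measures). Its definition has three layers.

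- **Task list.** Adherence rests on "completion of three daily tasks (practice (± guided meditation), mood rating and journal entry") together with "2-weekly module-specific tasks", "totalling 69 tasks over the 21-day programme (63 daily+6 weekly").
- **Individual rule.** "Individual adherence is defined as completion of ≥48 tasks (≥70", with the percent sign closing the bracket.
- **Group rule.** "Intervention adherence success is defined as ≥70% of participants meeting this individual adherence threshold".

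Under Sample size: "A sample of 40 participants (20 per group) was chosen based on published guidance for early-phase trials". Under Analysis strategy and missing data, the primary outcomes "will be summarised as frequencies and proportions", using the data available and without imputation. Further outcome detail is referred to supplement S5, which is not at hand.

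**The concern.** The individual rule is written twice in one sentence, as a count and as a percentage, each with a greater-than-or-equal sign. Both forms can be coded directly. One analyst could test whether tasks are at least 48, another whether tasks divided by 69 are at least 0.70. Each would be following the text, yet they would classify a participant with 48 tasks differently.

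That classification is the only input to the group success rule. If the ambiguity stays open until the data are in, the choice between the two forms could be made with the result in view. If the count is used, a report that adherent participants completed at least 70% of tasks would be untrue for anyone at 48.

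**Working it through.** **Inputs** (Outcome measures, unless noted): three daily tasks, 21 days, two module tasks per week, stated total 69, cut-off 48 or 70%, group rule 70%, and 40 participants (Sample size).

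**1. The denominator reproduces.** Daily: 3 × 21 = 63. Weekly: 2 × 3 weeks = 6. Total: 63 + 6 = 69, as stated. The stated 6 weekly tasks also show that the module tasks are two per week, not one every two weeks.

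**2. The cut-off reproduces only with rounding.** 0.70 × 69 = 48.3. To the nearest task, or rounded down, this is 48. A strict minimum needs rounding up, which gives 49.

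| Tasks | Share of 69 | Adherent by count (≥48) | Adherent by percentage (≥70%) |
|---|---|---|---|
| 47 | 68.12% | no | no |
| 48 | 69.57% | yes | **no** |
| 49 | 71.01% | yes | yes |

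The rules differ at 48 and nowhere else.

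**3. The group rule has no rounding problem at 40.** 0.70 × 40 = 28 exactly. Each participant is 1/40 = 2.5 percentage points. Let A be the number with 49 or more tasks and k the number with exactly 48. The verdict depends on the form used only if A ≤ 27 and A + k ≥ 28. With k = 1 this means A = 27: 27/40 = 67.5% (fail) against 28/40 = 70% (pass).

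**4. How often this could matter.** The article gives no expected completion rate, so the following rests on assumed values. Let X be a participant's completed tasks out of 69. The chance of group success is P(Bin(40, p) ≥ 28), with p = P(X ≥ 48) or p = P(X ≥ 49). X is binomial if tasks are independent. Otherwise it is beta-binomial, with mean m and correlation ρ between tasks of the same participant (parameters ms and (1 − m)s, where s = 1/ρ − 1).

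| Mean completion | ρ | P(X = 48) | P(success), ≥48 | P(success), ≥49 |
|---|---|---|---|---|
| 70% | 0 | 0.104 | 0.103 | 0.005 |
| 70% | 0.1 | 0.034 | 0.060 | 0.023 |
| 70% | 0.3 | 0.017 | 0.105 | 0.072 |
| 80% | 0 | 0.013 | 1.000 | 1.000 |
| 80% | 0.1 | 0.024 | 0.963 | 0.918 |
| 80% | 0.3 | 0.013 | 0.811 | 0.754 |
| 90% | 0.1 | 0.008 | 1.000 | 1.000 |
| 90% | 0.3 | 0.007 | 1.000 | 1.000 |

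With ρ of 0.1 to 0.3 and mean completion of 60% to 90%, P(X = 48) runs from 0.7% to 3.4%. In 40 participants that is an expected 40 × 0.007 = 0.3 to 40 × 0.034 = 1.4 people at exactly 48.

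**The case against.** The strongest reply is that 48 is plainly the rule and the bracket is its rounded label: 48.3 rounds to 48 tasks, and 69.57% prints as 70%. This very likely explains where the number came from, and it stands to the extent that the count can be applied alone without any gap. It does not make the two forms agree. The bracket carries a minimum sign, no rounding convention is stated, and the next sentence uses the same 70% minimum for the group, where 28 of 40 meets it exactly.

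The second reply also stands: little depends on this. The primary outcomes are summarised descriptively, no formal power calculation was done, and no interim analysis is planned, so no error rate or sample size rests on the cut-off. The largest shift in the table needs independent tasks and a mean completion of 70%, right at the cut-off.

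A reader might infer that the primary success rule itself is wrong. The documents do not support that. The group criterion contains no arithmetic error, and the individual criterion includes a usable integer. A reader might also infer that 49 must be the intended number. Nothing in the article shows that the percentage was meant to override the count.

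**Conclusion.** The count and the percentage in the individual adherence rule are inconsistent by one task: 48/69 = 69.6% against a stated minimum of 70%, which needs 49/69 = 71.0%. This follows from the article's own figures and needs no assumption.

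It is a minor inconsistency in the threshold of a primary feasibility outcome. It can alter the adherence verdict only if at least one participant has exactly 48 tasks and the group proportion sits at the line. Under the assumed correlated-task scenarios, the chance of declaring success differs between the two forms by up to about 6 percentage points (0.811 against 0.754) and by almost nothing at 90% completion.

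The line of 28 assumes that all 40 participants are counted. The article does not say who forms the adherence denominator, so with a different number analysed the line moves.

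**What to change.** Before adherence data are summarised, state one governing integer and drop the conflicting form. Either wording resolves the point:

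- *At least 49 of 69 tasks (71.0%).* This keeps the stated 70% minimum and makes the criterion slightly stricter.
- *At least 48 of 69 tasks (69.6%).* This keeps the prespecified count and removes the claim of at least 70%.

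Use the chosen integer in the analysis, and check any other place where the threshold is recorded, such as supplement S5. The edit is one number or one label. The Ethical approval section sends important changes, including changes to outcomes, to the ethics committee before they take effect, so raising the count to 49 may need that step. Correcting the label is the lighter change.
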